### Sensitivity Analyses

A formal sensitivity analysis will be performed to address potential protocol deviations and data completeness variations. The primary longitudinal analysis (pairwise deletion tracking available cases) will be cross-verified against a conservative BOCF model. In this sensitivity check, any missing or protocol-deviated postintervention slot will be replaced directly with that participant’s baseline value, representing an assumption of zero therapeutic efficacy. The *P* values from both the primary available-case model and the secondary BOCF imputation model will be compared; if the statistical significance (*P*<.05) remains consistent across both frameworks, the biological findings of the trial will be considered methodologically stable and free from attrition bias.

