### Outcome Measures

#### Primary Outcome

The primary outcome is a decrease in serum MDA levels and increase in serum SOD values. A significant reduction in serum MDA values (baseline and postintervention), indicated by a *P* value <.05, along with a moderate to large Cohen *d* value suggesting a meaningful change will indicate a reduction in oxidative stress levels. A significant increase in SOD activity (baseline and postintervention), indicated by a *P* value <.05, along with a moderate to large Cohen *d* value suggesting a meaningful change reflects an enhanced biological defense mechanism and improved metabolic resilience following the therapy.

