### Sample Size

The sample size is feasibility-driven. It was chosen based on pragmatic constraints. As this is an exploratory study, the goal is not to achieve definitive statistical power but to establish a foundation for future, larger-scale confirmatory research. Analyzing the census of Kerala, only 30% of the population could be sampled as healthy volunteers excluding NCDs, infectious diseases, other systemic illness like cancer, and age. The sample size was calculated as 53 using the following formula;

$$n=\frac{Z_{1-\alpha /2}^{2}\times P(1-P)}{d^{2}}$$

where Z_1-α/2_=1.96 (assuming a 95% CI), *P*=.5 (expected effeciency/anticipated proportion), and d=0.15 (15% margin of error), assuming a dropout rate of 20%.

Although this sample size is rooted in regional screening feasibility, a retrospective sensitivity power analysis confirmed that a finalized cohort of 53 individuals provides 80% statistical power (*α*=.05) to detect a small-to-medium intra-individual effect size (Cohen *d*=0.395) using a 2-sided paired samples framework. This standard biostatistical validation confirmed that, although the enrollment target is grounded in regional fieldwork constraints, it remains mathematically sensitive enough to capture subtle, homeostatic optimization trends in continuous aging biomarkers (MDA, SOD, and telomerase activity) within a healthy cohort.

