### Statistical Measures

The change in values of the outcome measures including MDA, SOD, telomerase activity, and telomere length will be recorded. The data will be tested for normality using the Shapiro-Wilk test. They will be tested for significance using paired *t* tests (if the data are normally distributed) or the Wilcoxon Signed Rank test (if the data are not normally distributed). A *P* value <.05 will be considered significant. All statistical analysis will be conducted using SPSS version 31 (IBM Corp). Moreover, a secondary exploratory subgroup analysis will be conducted within and between the 2 cohorts (*Vamana* and *Virechana* groups) based on the distribution of the data. If the data are normally distributed, within-group analysis will be conducted using paired *t* tests and between-group analysis will be conducted with *t* tests, whereas Wilcoxon Sign Ranked tests and Mann-Whitney *U* tests will be used, respectively, for data that are not normally distributed.

Cohen *d* effect sizes will also be calculated to address the exploratory nature of the study and evaluate the clinical and biological relevance of changes in biomarkers (ie, MDA, SOD, and telomerase activity). Results will be interpreted based on the magnitude and directionality of these effect sizes (small: 0.2; medium: 0.5; large: 0.8) to provide a standardized measure of treatment impact beyond simple *P* value testing.

Given the exploratory, hypothesis-generating design of this pilot study, secondary multivariable analyses will be introduced to evaluate the influence of potential baseline confounders. For normally distributed continuous data, an analysis of covariance (ANCOVA) will compare postintervention outcomes between the 2 seasonal subcohorts (*Vamana* vs *Virechana*) using individual pre-intervention scores as the baseline covariate to mathematically adjust for initial biological variation. Additionally, to evaluate the entire cohort of 53 participants as a unified group, multiple linear regression models will be constructed using the postintervention scores as the dependent variable, entering baseline biomarker values, age, sex, and baseline BMI as independent predictors to systematically control for demographic and physical confounding variables.

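### The stability rule re-checks only P<.05 under BOCF, although a finding is defined by P<.05 together with a moderate-to-large Cohen d

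*Protocol article*

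**What the plan says.** For MDA and SOD, the Primary Outcome section of the protocol article requires a P "value <.05, along with a moderate to large Cohen" d before a change is read as meaningful. The Secondary Outcomes section uses the same pairing for telomerase. Statistical Measures gives the scale, "small: 0.2; medium: 0.5; large: 0.8", and explains that d is there "to provide a standardized measure of treatment impact beyond simple" P value testing.

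The Sensitivity Analyses section sets the available-case analysis against a BOCF analysis in which missing or protocol-deviated post-intervention values are replaced by the participant's baseline. It then fixes a decision rule: the P "values from both the primary available-case model and the secondary BOCF imputation model will be compared; if the statistical significance" at P<.05 "remains consistent across both frameworks, the biological findings of the trial will be considered methodologically stable and free from attrition bias". Cohen d does not appear in that rule.

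Two rates bear on the size of the problem. Statistical Handling of Missing Data expects less than 5% missing. The Sample Size section works from "assuming a dropout rate of 20"%.

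**The concern.** The definition of a finding has two parts, and the rule that certifies its stability tests one of them. The untested part is the one that zero-change imputation affects. A marker could meet the definition on available cases, miss the effect-size part under BOCF, and still be reported as a stable, meaningful change. Future Directions intends to use this trial's effect sizes to design the next one, so how far d depends on the handling of missing values is worth showing.

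**Working it through.** **Inputs.** From the Sample Size section: N = 53, two-sided α = .05, paired framework, detectable d = 0.395, dropout 20%. From Statistical Handling of Missing Data: under 5% missing, so at most 2 of 53. From Statistical Measures: medium d = 0.5.

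**Assumptions.** Moderate is read as medium, with a cut-off of 0.5. The protocol names no standardiser, so d is taken as mean change divided by SD of change, in the hoped-for direction. Changes are normal, the paired t test is used, and values are missing completely at random.

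**The plan's own figures.** 1.96² × 0.5 × 0.5 / 0.15² = 42.68, and 42.68 / 0.8 = 53.36, which agrees with 53. A noncentral t calculation with N = 53 and d = 0.395 gives 80.6% power, against the stated 80%. Both reproduce.

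**What P<.05 requires.** The critical t on 52 df is 2.007, so the smallest significant d is 2.007 / √53 = 0.276. Under BOCF, every d between 0.276 and 0.5 keeps significance and misses the effect-size criterion.

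**What BOCF does to d.** Let n changes be observed with mean d and SD 1, and let k changes be set to zero, with N = n + k = 53:

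- M = n·d / N
- V = [(n − 1) + n·d² − N·M²] / (N − 1)
- d_BOCF = M / √V, and t_BOCF = d_BOCF × √N

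**Example: n = 42, k = 11, d = 0.55.** M = 42 × 0.55 / 53 = 0.4358. V = (41 + 12.705 − 10.068) / 52 = 0.8392. d_BOCF = 0.4358 / 0.9161 = 0.476. The available-case t is 0.55 × √42 = 3.56 (P = .0009); the BOCF t is 0.476 × √53 = 3.46 (P = .0011). The rule calls this stable although d is now below 0.5.

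**An available-case d of exactly 0.50:**

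| Replaced (k of 53) | d_BOCF | P available-case | P BOCF | Available-case d that drops below 0.5 |
|---|---|---|---|---|
| 2 (3.8%) | 0.488 | .0008 | .0008 | 0.500–0.512 |
| 5 (9.4%) | 0.471 | .0012 | .0012 | 0.500–0.532 |
| 11 (20.8%) | 0.435 | .0024 | .0026 | 0.500–0.580 |

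d_BOCF rises with d, so with 11 replaced every result with d of at least 0.5 ends at 0.435 or more, above 0.276. None can lose P<.05. Starting from d = 0.50, 35 of 53 values must be replaced before the BOCF P passes .05 (d_BOCF 0.274, P = .051).

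**How often this happens.** On available cases d ≥ 0.5 already implies P<.05 (the critical d with 42 pairs is 0.312), so success is simply d ≥ 0.5. With the noncentral t distribution and a true d of 0.5:

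| k | Trials meeting the definition | Of all trials, d lost under BOCF | Share of successes |
|---|---|---|---|
| 2 | 51% | 3% | 6% |
| 5 | 51% | 8% | 16% |
| 11 | 51% | 18% | 36% |

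The share depends on the true effect. With k = 11 it is 48% of successes (13% of all trials) at a true d of 0.395, 24% (18%) at 0.6 and 6% (6%) at 0.8. With k = 2 the share of all trials is 2% to 3% for true d from 0.395 to 0.6.

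**The case against.** **The expected rate is low.** The section that plans for missing data expects under 5%, and Expected Completion ends the trial only when 53 volunteers have completed all evaluations. That fits poorly with 42 pairs plus 11 replaced values. This stands: the small band at k = 2 is the leading case. Two things keep the larger cases relevant. The protocol itself uses 20% dropout, and its BOCF rule also replaces protocol-deviated values, for which no rate is given, so the replaced share may exceed the missing share.

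**The cut-off is softer than a pass mark.** Primary Outcome gives no number, and the 0.2/0.5/0.8 values are benchmarks for interpretation in a study described as exploratory. This stands for the exact bands. The mismatch between a two-part definition and a one-part check does not depend on where the line falls.

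**BOCF lowers d mechanically.** With values missing completely at random, as the protocol assumes, the available-case d is not biased by dropout; d falls because zeros are inserted. This stands. A reader might infer that dropout is distorting the result, or that a d below 0.5 under BOCF proves a finding is not robust. The documents support neither, so a hard pass/fail line on the BOCF d would be too strong.

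**The full plan may report d under BOCF.** It may, and a condensed article need not list every output. A reader might infer that d will never be recomputed; the text does not say so. What it does fix is that the stability label turns on P alone.

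**Conclusion.** The concern holds, as a minor one. The stability rule can call a finding stable when, under the same BOCF analysis, it no longer meets the trial's own definition of a finding. For results that meet that definition, the P comparison can hardly fail at any plausible amount of missing data, so agreement of P values is little evidence of stability and cannot show absence of attrition bias.

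At the planned missing rate the consequence is confined to an available-case d within about 0.012 of the cut-off. It becomes material only if the replaced share approaches the 20% in the sample-size calculation. The percentages of successes apply only to trials that met the definition; the share of all trials is the fairer measure of how often this would occur. All sizes rest on the standardiser, cut-off, t-test and missingness assumptions listed with the calculation. The primary estimate is unaffected.

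**What to change.** In Sensitivity Analyses, report for each marker the mean change with 95% CI, Cohen d and P under both the available-case and the BOCF analysis, and name the standardiser for d. Base the stability statement on both parts of the definition in Primary Outcome and Secondary Outcomes. Where d leaves the moderate range under BOCF, state that the effect-size criterion depends on the missing-data assumption instead of calling the finding stable. Delete the claim that agreement shows freedom from attrition bias.

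The cost is about one sentence and one extra table column, and the Results section says data analysis is still pending. The downside is that some borderline findings will carry a qualified statement even when missingness caused no bias.

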### Statistical Handling of Missing Data

This trial evaluates objective biochemical endpoints within a strictly monitored hospital inpatient setting; the incidence of missing data is anticipated to be extremely low (<5%). Any missing data points are assumed to follow a missing completely at random mechanism, as data omissions would stem strictly from random logistical or laboratory anomalies.

Missing data will be handled using an available case analysis (pairwise deletion) framework for the primary longitudinal comparisons, ensuring that all available valid pairs of pre- and postintervention biochemical metrics are fully utilized without fabricating data. To verify that this approach does not introduce statistical bias, a conservative baseline observation carried forward (BOCF) sensitivity analysis will be executed concurrently. Under the BOCF framework, any missing postintervention value will be replaced by the participant’s own baseline value, assuming zero therapeutic change. This dual-validation approach guarantees a highly transparent, noninflationary evaluation of the trial’s biochemical endpoints.

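### Agreement of P values between the available-case and BOCF analyses is near-automatic in a single-group paired test, so it cannot support a conclusion of no attrition bias

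*Protocol article*

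**What the plan says.** The Statistical Handling of Missing Data section makes available-case analysis primary, assumes data are missing completely at random and expects under 5% missing. To verify that this introduces no bias, it adds that "a conservative baseline observation carried forward (BOCF) sensitivity analysis will be executed concurrently", with each missing post-intervention value replaced by the participant's own baseline. It then asserts: "This dual-validation approach guarantees a highly transparent, noninflationary evaluation".

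The Sensitivity Analyses section turns this into a decision rule. Missing or protocol-deviated post-intervention values are set to baseline and the two P values are compared. The rule reads: "if the statistical significance (*P*<.05) remains consistent across both frameworks", then "the biological findings of the trial will be considered methodologically stable and free from attrition bias".

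The test is a single-group comparison of paired values. Under Statistical Measures: "They will be tested for significance using paired *t* tests (if the data are normally distributed) or the Wilcoxon Signed Rank test", the choice being made by Shapiro-Wilk. The Participant Retention and Discontinuation Protocols section retains only baseline biomarkers for participants who withdraw or deviate.

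**The concern.** A sensitivity analysis is informative only if it could come out differently when the primary assumption is wrong. Here the alternative assumption (zero change for everyone missing) is judged solely by whether P stays on the same side of .05. In a one-sample test, added zeros dilute the numerator and the denominator of the test statistic together, so the criterion hardly responds to them. The trial could then report that attrition bias has been excluded on the strength of a check that could not have found it. The P<.05 criterion is half of the success definition under Primary Outcome, so the false reassurance would attach to the main result.

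**Working it through.** **Inputs.** N=53 and 2-sided alpha .05 (Sample Size, Sensitivity Analyses); paired t or Wilcoxon signed-rank test (Statistical Measures); missingness under 5%, so at most 2 of 53 (Statistical Handling of Missing Data); 20% dropout, about 11 of 53 (Sample Size).

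**The plan's own figure.** Sample Size says that "a finalized cohort of 53 individuals provides 80% statistical power" for d=0.395, "using a 2-sided paired samples framework". The noncentral t gives 0.806, so this reproduces and the one-sample framework below is the plan's own.

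**Algebra.** Let S be the sum and Q the sum of squares of the observed changes, and r = S²/Q. For n changes, t² = (n−1)r/(n−r). Appended zeros leave S, Q and therefore r unchanged. Only n moves, from the number of completers m to 53, and the degrees of freedom from m−1 to 52.

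- *2 missing (m=51), available-case P=.0500:* t=2.0086 and r=3.808. With n=53, t² = 52×3.808/(53−3.808) = 4.025, so t=2.0063 and P=.05004.
- *11 missing (m=42), available-case P=.0500:* t=2.0195 and r=3.800. With n=53, t² = 52×3.800/(53−3.800) = 4.016, so t=2.0041 and P=.0503.

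| Available-case P | BOCF P, 2 missing | BOCF P, 11 missing |
|---|---|---|
| .0500 | .05004 | .0503 |
| .0100 | .01006 | .0104 |
| .0010 | .00102 | .0011 |

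Significance flips only if the available-case P lies between .04996 and .0500 (2 missing) or between .0497 and .0500 (11 missing).

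**Wilcoxon.** With the usual dropping of zero differences (assumed), the appended zeros are discarded and P is identical. In an example with 11 zeros it was .019056 both ways.

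**What BOCF does change.** The mean change is multiplied by 51/53 = 0.962 or 42/53 = 0.792. An available-case d of 0.50 becomes 0.488 or 0.435. The rule uses neither.

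**Can the rule see attrition bias?** Simulation with the SD of change set to 1:

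- True mean change 0, and 11 dropouts all from the lower half of changes: both analyses are falsely significant in about 26.8% of trials, and they disagree in 0.06%.
- Completers with d=0.45 and withdrawn participants truly worsening by 0.5 SD: the t-test verdicts agree in more than 99.9% of trials. The share that passes the check as significant, although all 53 would give P≥.05, is about 5% with 2 missing and about 42% with 11.

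**Test switching.** If Shapiro-Wilk is reapplied to the BOCF data (the plan does not say), the spike of zeros can change which test is used. Verdicts then disagree in about 2–3% of trials with 11 zeros and about 0.1% with 2.

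**The case against.** A reader might infer that the check literally cannot fail. That goes too far. There is the narrow band just under .05, and there is possible test switching by Shapiro-Wilk. The rule also covers protocol-deviated values: if a deviator's observed post-intervention value were in the primary analysis and BOCF overwrote it, disagreement at d=0.395 would be about 5% with 2 deviators, 8% with 5 and 15% with 11. The Participant Retention section appears to close that last route, because only baseline biomarkers are kept for deviators. None of the three routes detects attrition bias: the first is rounding at the threshold, the second is noise from choosing a test, and the third reflects deviation.

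A reader might also infer that BOCF is not conservative at all. It is conservative for the mean change and for Cohen d, and the plan does report mean change with a 95% CI and does require a moderate to large d. It is not conservative for the P value, which is all that the rule compares.

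The 42% figure should not stand alone. It needs 11 missing, whereas the missing-data section expects at most 2, where the figure is about 5%. It also counts worsening after withdrawal, which is not the target of the While-On-Treatment strategy under Handling of Intercurrent Events. That section names multiple imputation as well, so BOCF is not the only missing-data device in the article.

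Finally, the trial is exploratory and the primary estimate does not depend on BOCF. Both are true, and they limit the damage. They do not justify a pre-declared conclusion that the check cannot support.

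**Conclusion.** The decision rule is wrong as written. Equal P<.05 status in the two analyses is near-automatic and is almost no evidence about attrition bias, at either level of missingness that the article mentions. The t-test result is algebraic; the Wilcoxon result assumes that zero differences are dropped. The practical harm depends on how many values are missing and how those participants fared. It is small if the under-5% expectation holds and substantial if the 20% allowance is used up by participants who worsened. Nothing in the article shows that attrition bias will occur. The point is that this rule would not reveal it, and the assurance should not be promised.

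**What to change.** In Sensitivity Analyses, replace the P-value agreement rule with a side-by-side report of mean change, 95% CI and Cohen d from the available-case and BOCF analyses. Add a short delta (tipping-point) analysis: shift the imputed changes of missing participants adversely in steps, past zero change into worsening, and report the shift at which the CI first includes zero. With no missing values it is not needed; with 1 or 2 it takes a few lines.

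Remove the conclusion "the biological findings of the trial will be considered methodologically stable and free from attrition bias" and the guarantee in "This dual-validation approach guarantees a highly transparent, noninflationary evaluation", and restrict the description of BOCF as conservative to the effect estimate. The cost is a few lines of analysis code and a more modest claim, with no new data. The Results section says the analysis is still pending, so the change can be specified beforehand.

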### Dissemination Policy

On completion of the trial and data analysis, we will ensure that the evidence gathered reaches health care professionals and scientific community through all possible ways. We will make sure that the same information reaches the public in appropriate ways to be incorporated as a preventive strategy for age-related changes and improving the health span. The study results will be submitted to peer-reviewed journals for publication regardless of the findings. Moreover, the results will be presented at relevant academic and scientific conferences. The CTRI page will also be updated accordingly upon completion of the study.

## Results

The study started recruiting participants in March 2025, and, as of April 4, 2025, 27 participants had voluntarily participated in *Vasantha Vamana*. The data analysis is pending. We expect to reach the targeted number of participants by December 2026. The data analysis will be conducted, and the results will be submitted for publication within the 6 months following study completion.

## Discussion

### Theories Underpinning the Study

*Ritu sodhana* or seasonal purification is generally intended to eliminate the seasonal accumulation of humors. This process thereby reduces the susceptibility of seasonal disorders [14]. Acharya Charaka in the context of *Ritu sodhana* has put forth an additional statement that administration of seasonal biopurification will bestow rejuvenation and improve health span [19]. Even though these procedures have been evaluated for their clinical efficacies, its influence on biomarkers for aging has not yet been evaluated. This gap underpins the development of this research protocol, which aims to generate preliminary evidence for this purpose.

*Trikatu Churna,* used for *pachana* and *deepana*, has bioactive constituents including piperine, gingerols, and shogaols and has demonstrated effects on gastric secretion, gut motility, enzymatic activity, splanchnic circulation, and nutrient bioavailability, supporting improved digestive efficiency and systemic absorption [20,21]. This serves as metabolic priming, which is essential to ensure effective digestion and absorption prior to the administration of ghee. *Moorchita ghruta* [22] is widely used in clinical practice. Since the cohort includes healthy volunteers, no other medicated ghee was chosen. *Moorchita taila* [23] was chosen for external application owing to its popularity for the panchakarma procedure. *Trivrut lehya* is used for *Virechanakarma* with limited complications [24].

Based on this framework, we expect that *sodhana* will aid with releasing the waste metabolites, thereby influencing the values of MDA, SOD, and telomerase activity to trigger measurable anti-aging pathway responses across our cohort of 53 healthy volunteers. The hypothesized primary findings include a statistically significant pre-to-postintervention drop in oxidative tissue damage evidenced by a reduction in MDA levels coupled with a significant upregulation of cellular antioxidant defenses, marked by enhanced SOD activity. Furthermore, it is anticipated that this intensive detoxification phase will positively modulate cellular longevity clocks, manifesting as stabilized or elevated telomerase activity, thereby providing an objective, molecular validation of Acharya Charaka’s classical rejuvenation hypothesis.

There are multiple theories supporting the process of aging. However, evidence for the molecular, cellular, or physiological changes involved in the process of aging and the associations among them is lacking [25]. Oxidative damage is one theory for aging. The multiple interrelated reactions involved in metabolism generate reactive oxygen species (ROS) in the body. The hypothesis that ROS accelerate the aging process is supported by genetic studies of transgenic animals engineered to overexpress or lack antioxidant enzymes. A study concluded that the life span of *Drosophila melanogaster* is extended by the overexpression of antioxidants including SOD and catalase [26]. MDA is also a widely used biomarker indicating lipid peroxidation, yet another oxidative degradation phenomenon enhancing aging. However, MDA is a stable end-product of lipid peroxidation. Therefore, it can be considered a reliable and noninvasive indicator of cumulative oxidative damage to cell membranes. SOD provides a real-time view of the body’s redox state. Unlike other aging biomarkers, it responds dynamically to changes in oxidative load [27].

Biomarkers including MDA and SOD are intended as short-term surrogate indicators of oxidative stress. They are not direct measures of aging. In a sample of 43 relatively healthy individuals, a 21-day fasting period influenced the levels of blood oxidative stress biomarkers including MDA [28]. In addition, a 30-day, high-intensity, interval running training course proved to be more effective at reducing MDA levels and increasing SOD levels in young men [29]. These existing data demonstrate that a 21-day to 30-day intervention window is physiologically sufficient to induce significant, measurable alterations in human blood oxidative stress parameters. Consequently, these established timelines provide strong chronological justification for the 21-day duration of our intensive inpatient *Śodhana* protocol, confirming that our study window is fully optimized to capture variations in the biomarkers.

Due to end-replication problems, telomeres are shortened after each cell division. As such, telomere length is regarded a marker of aging. Telomere integrity largely depends on telomerase activity [30]. Therefore, enhancing telomerase activity is the target of many therapeutic approaches aiming to maintain telomere length and thereby by regulating the cellular heath span. The telomerase enzyme counteracts telomere attrition by catalyzing the addition of TTAGGG nucleotides to the chromosome end [30,31].

Incorporating variables like MDA, SOD, and telomerase activity enable us to strengthen the theories documented in traditional texts by generating hypotheses based on scientific evidence. This study will serve as a feasibility trial, generating data that could inform larger clinical trials.

